# Protocol for the STAR (Sheffield Treatments for ADHD) project: an internal pilot study assessing the feasibility of the Trials within Cohorts (TwiCs) design to test the effectiveness of interventions for children with ADHD

**DOI:** 10.1186/s40814-018-0250-3

**Published:** 2018-03-02

**Keywords:** ADHD, Feasibility, TwiCs, Nutrition, Homoeopathy

## Abstract

**Background:**

Attention deficit hyperactivity disorder (ADHD) is a common and growing problem and a leading cause of child referrals to Child and Adult Mental Health Services (CAMHS). It is a drain on resources across nationally funded support agencies and associated with negative outcomes such as early criminality, school disruption and antisocial behaviour. Mainstream interventions (pharmacological and behavioural) demonstrate effectiveness whilst implemented, but are costly, often have unwanted side effects and do not appear to be affecting long-term outcomes.

Development of a robust evidence base for the effectiveness of current and novel interventions and their impact over the long term is required. The aim of the Sheffield Treatments for ADHD Research (STAR) project is to facilitate a rigorous evidence base in order to provide information about the comparative (cost) effectiveness and acceptability of multiple interventions to key stakeholders.

**Methods:**

The Trials within Cohorts (TwiCs) design was used to build a cohort of children with a diagnosis of ADHD and conduct a three-armed pilot trial of the clinical and cost effectiveness of two novel interventions: (a) treatment by nutritional therapists and (b) treatment by homoeopaths, compared to (c) treatment as usual.

Participants are recruited to the STAR long-term observational cohort, and their outcomes of interest (ADHD symptoms, health-related quality of life, school disruption, resource use and criminality) are measured every 6 months by carers and (blinded) teachers. Two promising interventions were identified for the first randomised controlled trial embedded in the cohort. A random selection of eligible participants is offered treatments (a) and (b). The outcomes of those offered treatment are compared to those not offered treatment using intention to treat (ITT) analysis.

The feasibility of recruiting to the cohort and the trial, delivering the interventions, the effectiveness of the interventions and the appropriateness, sensitivity and collectability of outcomes is trialled.

**Discussion:**

The results of this trial will provide information on the feasibility of the TwiCs design to facilitate multiple trials of potential interventions for children with ADHD, and the acceptability, clinical and cost effectiveness of two potential interventions for ADHD to ADHD stakeholders including service providers. Future stages of the STAR project will test other treatments informed by the results in stage 1.

**Trial registration:**

ISRCTN number 17723526. 10.1186/ISRCTN17723526. Date assigned 27/4/15.

## Background

ADHD is a common and growing problem and a leading cause of child referrals to Child and Adult Mental Health Services (CAMHS). It accounts for a sizeable amount of resource use, is a drain on resources across nationally funded support agencies [1], and presents a major, often unmet challenge to services [2]. There is a need to improve outcomes, where the condition is associated with negative outcomes such as early criminality, school disruption and antisocial behaviour. Mainstream interventions (pharmacological and behavioural) demonstrate effectiveness whilst implemented, but are costly, often have unwanted side effects and do not appear to be affecting long-term outcomes.

ADHD is associated with a range of negative behaviours such as difficulties regulating emotions, particularly anger [3], involvement with violent criminality and at a young age [4], school disruption, exclusion and low attainment [5, 6]. Children often have few friends [7], and their experience of school can be one of academic failure, rejection by peers and low self-esteem [8]. Information is required about cost-effective interventions which can achieve positive changes over the long term.

Current interventions may only be effective whilst implemented [9, 10] over the short term [11–13] and compliance with medication (the main intervention) can be poor [14, 15]. Furthermore, up to 25% of children may not respond to stimulant medication [16–18] which is associated with adverse events [19] particularly those with concomitant ADHD and autism spectrum conditions (ASCs) [20–22].

Whilst we have information about the efficacy of mainstream interventions, it is unclear whether this translates into real-world effectiveness, acceptability and improvement in long-term outcomes. Pragmatic trials will be helpful for a variety of reasons [23]. Measurement of the acceptability and (cost) effectiveness of interventions over the long term can provide important information for stakeholders. Heterogeneity is a feature of ADHD expression and children often have a wide range of other diagnoses such as ASCs [24], conduct disorders [25], sleep disturbance [26], gut dysbiosis and tics [27]. Information is required about whether efficacious interventions for children with single ADHD diagnoses are effective in populations with additional co-morbidities. Finally, children with ADHD and their families can be hard to engage and treat [28]; therefore, the acceptability of interventions is an important consideration.

The Trials within Cohorts (TwiCs) design (also known as the cohort multiple randomised controlled trial (cmRCT) design) has been developed to help address some of the limitations associated with existing RCT designs [29]: for example, the tendency for potential treatments to be trialled one at a time, in different populations by different research teams, yielding trials with heterogeneous trial populations between trials and often short-term and heterogeneous outcomes.

The TwiCs design recruits a large, long-term observational cohort of people with the condition of interest and regularly measures their outcomes of interest. For each trial embedded within this cohort, a proportion meeting trial inclusion and exclusion criteria are offered interventions. Those not randomly selected act as a virtual treatment as usual (TAU) control group.

The STAR project aims to facilitate a rigorous evidence base in order to provide information about the comparative (cost) effectiveness and acceptability of multiple interventions to key stakeholders about interventions which might address treatment gaps. This pilot study addresses the research question: Is the TwiCs design feasible to assess the effectiveness of treatments for ADHD? For the study, two interventions with preliminary indications of effectiveness, considered complementary and alternative medicine (CAM) [30], have been selected. Parents of children with ADHD are trying these interventions, paying for them out of pocket.

CAM use for ADHD has been found to range from 12% [31] to 71% [32]. Its use is increasing, especially for conditions without effective recommended treatments, where medical treatment is associated with serious adverse effects [33] and for children with chronic conditions [34–36]. Patients are using CAM despite physician’s concerns, and in addition to medication, therefore, development of a robust evidence base is required. The CAM interventions being used by parents of children with ADHD include acupuncture, aromatherapy, chiropractic, elimination diets, fatty acid supplementation, herbal medicine, homoeopathy, massage, speech, physical and occupational therapy, and vitamins [31, 32, 36, 37].

For this first RCT, we identified two interventions showing indications of effectiveness and being used by parents of children with ADHD. Since they are being tested as experienced in real-life clinical practice as befitting a pragmatic trial, we named them treatment by a homoeopath and treatment by a nutritional therapist.

The published evidence for homoeopathic treatment for ADHD consists of seven trials: two RCTs tested the efficacy of specific homoeopathic formulas [38, 39]; four RCTs tested the efficacy of individualised homoeopathic medicines [40–43]; and one within subjects trial of children with ASCs measuring ADHD symptoms tested the effectiveness of individualised homoeopathic treatment [44]. All studies but one [42] of individualised homoeopathy found significant improvements, but effect size varied, and quality is variable.

Although a healthy diet is recommended by NICE [2], no trials assessing the effectiveness or acceptability of this have yet been conducted. There are many studies exploring the efficacy of individual nutrients, multiple nutrients, and special diets for ADHD. Systematic reviews concur that polyunsaturated fatty acids have small effects on ADHD symptoms [45, 46] and that restricted elimination diets, artificial food colour elimination and dietary supplements may be efficacious, but more studies are required before firm conclusions can be reached. Improvements may be optimised by both eliminating aggravating factors and boosting nutritional deficits in an individualised way, since sensitivities are found in some but not all children with ADHD. Treatment by nutritional therapists provides advice about, and support implementing, individually tailored exclusion, supplementation, and healthy eating.

### Aims and objectives

The aim of the STAR project is to provide a facility for efficiently testing multiple interventions for children with ADHD.

Stage 1 of the STAR project will test the feasibility of the Trials within Cohorts (TwiCs) design and conduct a three-armed pilot trial of the clinical and cost effectiveness of two interventions: (a) the offer of a course of treatment by homoeopaths and (b) the offer of a course of treatment by a nutritional therapist, compared to (c) treatment as usual.

Stage 1 will test the feasibility of the TwiCs design by conducting a small-scale test of the methods and procedures and assess the acceptability, deliverability, clinical and cost effectiveness of treatment by homoeopaths and nutritional therapists for children with ADHD.

The objectives of stage 1 are to assess the feasibility of recruiting to time and target a cohort of children with a diagnosis of ADHD, their carers and teachers; the feasibility and acceptability of the study design; the feasibility, deliverability, safety and acceptability of the interventions; the suitability, acceptability and deliverability of the outcome measures; and to inform sample size calculation for a full trial (stage 2).

## Methods

### Recruitment

At least 140 children aged 5–18 with a diagnosis of ADHD and any accompanying co-morbidities are recruited to an observational cohort and their consent to participate in the cohort is sought by completion of a questionnaire with embedded consent to be contacted again. Their outcomes of interest are measured at recruitment (baseline) and every 6 months, via these questionnaires, which are completed by carers and blinded teachers. Carers of children with ADHD were involved in the selection of items for, design and pilot testing of the questionnaire, advised about recruitment and sat on the steering committee.

### Randomisation

After recruitment to the STAR cohort, a three-armed internal pilot trial is subsequently conducted whereby random selections of eligible children are offered either adjunctive treatment by homoeopaths (arm 1) or nutritional therapists (arm 2). Randomisation is computer generated by an independent statistician from the University of Sheffield and held in the locked drawer of a different statistician from the University of Sheffield. Stratifying factors are age (primary 5–11/secondary 12–18), medication status (yes/no) and ADHD severity (Conners global ADHD *T* score 80+/under 80) [47]. Participants fulfilling inclusion and exclusion criteria who consent to be contacted again are identified on recruitment to the cohort. Stratifying factors are extracted and emailed to the statistician holding the randomisation list, who randomly assigns them to one of the three groups and gives them a randomly generated three-digit code by which they are subsequently identified.

Carer and child’s consent to try treatments is sought at this stage. They are sent a letter of invitation for 1 year of treatment, which includes a statement that participants can withdraw at any time; a brief description of the treatment; requests the carer to ask their child if they are happy to participate; a consent form to treatment to be signed by carer and child and returned in a pre-paid envelope; and an email address and telephone number as an alternate means of contact. The PI then rings the participants up and asks if they have any questions; if they wish to participate (if their form has not yet been returned); and if they both consent, to their details being passed on to the therapist. In the absence of a returned ‘consent to treatment’ form, carer and child’s wish to participate on the telephone is taken as verbal consent. Consent forms are then signed at the first appointment with the therapist, who further explains what treatment will constitute, as befits usual practice. Appropriate marks by young children are taken as signatures. Those children not selected act as a treatment as usual control (arm 3).

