### Inclusion/exclusion criteria

Inclusion criteria for the STAR cohort are children aged 5–18 (inclusive) with a carer-reported diagnosis of ADHD (date, venue and diagnosing physician) and a carer-reported Conners Global Index (CGI) *T* score of at least 55 (denoting mild atypicality (Table 1). Inclusion criteria for the trial are a carer-reported CGI score of at least 65 (indicating a significant problem) (Table 1).

**Table 1 Tab1:** Interpretive guideline for Conners’ *T* scores and percentiles

*T* score	Percentile	Guideline
70+	98+	Markedly atypical (significant problem)
66–70	95–98	Moderately atypical (significant problem)
61–65	86–94	Mildly atypical (possible problem)
56–60	74–85	Slightly atypical (borderline)
< 30–55	< 2–73	Average (typical: should not raise concern)

Exclusion criteria to both cohort and trial are children below the age of 5 or adults over 18; children with terminal, severe, life-limiting conditions; and families where English is not written or spoken (as the project does not have funds to provide a translation service). Exclusion criteria to the trial are children currently receiving treatment by a homoeopath or a nutritional therapist and children with CGI *T* scores below 65.

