### Outcome measurement

Carers of children with ADHD are asked to complete carer questionnaires (CQs) sent to them by post or completed on-line (www.starsheffield.com).The CQ includes the 10-item Conners’ Global Index (CGI) [47]; the 18-item Swanson, Nolan and Pelham Teacher and Parent Rating Scale (SNAP) [51]; the 9-item Child Health Utility health-related quality of life (CHU-9) measure [52]; and questions about resource use. The last page asks for consent from carers and children to be contacted again, for their school to be contacted, personal and school contact details.

Where consent is given, schools are sent a teacher’s questionnaire (TQ) and an information letter. They are not informed about treatment allocation. The TQ includes the CGI, SNAP, and questions about school-specific resource use, attendance, disruption and exclusion. Schools which do not want to participate are not contacted again.

Control group participants are not informed that they have not been selected for a treatment but continue to be sent questionnaires at the same time intervals as treatment groups. CQs and TQs are sent out every 6 months to all cohort participants. Those refusing the offer of treatment are still asked to complete outcome measures as usual every 6 months and considered members of the offer group.

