### The interventions

Homoeopaths are registered with one of the four main bodies representing homoeopaths in the UK. Nutritional therapists are registered with the British Association of Applied Nutrition and Nutritional Therapy and are members of the Complementary and Natural Healthcare Council. All therapists are CRB checked, complete an on-line NSPCC child protection course (https://www.nspcc.org.uk/what-you-can-do/get-expert-training), attend a 1-day training course on risk and receive guidelines in management of ADHD and serious adverse events.

Both interventions are offered to participants for a maximum of 1 year consisting of a maximum of eight appointments. Consultations take place at Complementary Medicine Centres, participant’s homes or on-line. First consultations last for up to 1½ h and follow-ups last up to 40 min approximately every 6 weeks for up to 1 year resulting in a total of up to seven contact hours. Homoeopaths conduct fact-finding consultations on the basis of which they prescribe homoeopathic medicines, guided by underlying basic homoeopathic principles [53]. Treating ‘like with like’ is the core principle: that substances causing certain symptoms in healthy persons may cure those same symptoms in those who are ill. Nutritional therapists take an initial health history and discuss and agree with participants an appropriate range of options such as elimination diets, healthy food and menu options, reducing aggravators such as food colourings or sugar; improving fluids intake, lifestyle issues such as sleep; specific dietary intervention for symptoms; and supplementation.

At each consultation, therapists ask participants and/or their carer (dependent on age) to complete Measure Your Own Medical Outcome Profile (MYMOP) [54]. This patient generated outcome measure consists of 4 self-chosen items measured using a Likert-type scale of 0 (as good as it could be) to 6 (as bad as it could be): two symptoms considered most bothersome, an activity ADHD limits participation in, and well-being. Diminution of scores represents improvement. This personalised measure allows participants to select their key concerns and document how they change over time. It is a validated outcome measure considered appropriate to capture non-specific effects.

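### Allocation is per child with no household rule, so enrolled siblings could be split between an offer and treatment as usual (TAU); the likely effect is small and the remedy cheap

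*Protocol article*

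**What the plan says.** The Randomisation section makes the child the unit at each step. Treatment is offered to a selection of children ("random selections of eligible children are offered either adjunctive treatment by homoeopaths (arm 1) or nutritional therapists (arm 2"), and the remainder are the comparator: "Those children not selected act as a treatment as usual control (arm 3". The procedure is described in some detail: "Stratifying factors are extracted and emailed to the statistician holding the randomisation list, who randomly assigns them to one of the three groups". The factors are all child-level: "Stratifying factors are age (primary 5–11/secondary 12–18), medication status (yes/no) and ADHD severity". No family or household identifier is mentioned.

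The Inclusion/exclusion criteria look only at the child's own current therapy: "Exclusion criteria to the trial are children currently receiving treatment by a homoeopath or a nutritional therapist". Families are mentioned there only in connection with language. The regression under Statistical analysis adjusts for gender, baseline CGI and age, and has no family term.

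Three other statements bear on the point:

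- Outcome measurement sets a safeguard: "Control group participants are not informed that they have not been selected for a treatment".
- The offer goes through the carer. The invitation letter "requests the carer to ask their child if they are happy to participate", and a telephone call follows (Randomisation). Under Outcomes, the same carer is an unblinded rater of the primary CGI outcome, alongside a blinded teacher.
- Nutritional therapy can include "elimination diets, healthy food and menu options, reducing aggravators such as food colourings or sugar", and consultations may be held at home (The interventions).

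**The concern.** Followed as written, the procedure allocates two eligible siblings independently, because the statistician receives nothing that would link them. Two things can then happen in a split household.

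First, a carer who is offered treatment for one child and hears nothing about the other can work out that the second child was not selected. The safeguard for controls fails in that home, and the same person rates both children on the carer-reported primary outcome. This applies to either offer.

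Second, menus, sugar and food colourings are largely matters for the whole household. If the nutrition offer is taken up, a TAU sibling may receive part of the intervention. Individually prescribed homoeopathic medicines are not shared in the same way.

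What is at stake is the pilot SMD. It feeds the 0.3 progression criterion (Table 2) and the sizing of the full trial (Sample size). The cohort is also meant to host later trials, which would inherit the same gap.

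**Working it through.** **The plan's own figures.** These are not in dispute, and they set the scale.

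- Full trial at SMD 0.4, two-sided alpha 0.05, power 80%: n = 2(1.96 + 0.84)²/0.4² ≈ 98.1, rounded up to 99 per group. The plan says about 100.
- With 40% attrition: 100/0.6 = 166.7. The plan says 166.
- Pilot: 140 × 0.8 × 0.8 = 89.6, about three arms of 30.

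**Inputs that the document does not give (assumptions).**

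- Allocation is 1:1:1, and siblings are allocated independently.
- A share s of trial children have one enrolled sibling; s = 5–15% is used.
- A fraction c of the treatment effect reaches the TAU sibling; c = 1 is the worst case.

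**How often siblings are split.**

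- In different arms of any kind: 1 − 3 × (1/3)² = 2/3.
- One offered treatment and the other TAU: 2 × (1/3) × (2/3) = 4/9.
- Given a TAU child, the sibling is offered some treatment with probability 2/3, and nutrition with probability 1/3.

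**Controls unmasked.** s × 2/3 = 3.3% at s = 5% and 10% at s = 15%. Of 30 controls, that is 1 to 3 children.

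**Controls living with a child offered nutrition.** s × 1/3 = 1.7% to 5%, or 0.5 to 1.5 of 30. This counts offers. If only 30% accepted, the minimum for progression in Table 2, the range would be 0.5% to 1.5%, or 0.15 to 0.45 of a child.

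**Dilution of the nutrition contrast.** SMD = 0.40 × (1 − c × s/3), with full uptake and c = 1:

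| s | SMD | n per group | Power at 100 per group |
|---|---|---|---|
| 0% | 0.400 | 99 | 80.7% |
| 5% | 0.393 | 102 | 79.4% |
| 10% | 0.387 | 105 | 78.1% |
| 15% | 0.380 | 109 | 76.6% |

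Outside the assumed range, s = 30% with c = 1 gives SMD 0.360, n = 122 and power 72.1%.

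**Against pilot noise.** With 30 per arm, the standard error of the SMD is about √(2/30) ≈ 0.26, so the 95% half-width is about 0.51. The worst shift in the assumed range is 0.02.

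**Direction.** Dietary spill-over pulls the contrast towards zero. A carer who compares a treated with an untreated child may exaggerate it. The document gives no basis for netting these off.

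**The case against.** The strongest reply is that this is a silence in a condensed article. The handling of siblings could sit in the full protocol, no stated figure is wrong, and nothing says that any family enrols two children. Both would need a reported diagnosis, a CGI T score of at least 65 and consent to further contact. That stands as a limit on size and certainty. It does not remove the point, because the article describes what is sent to the statistician, and on that description siblings could not be kept together.

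A second reply concerns masking. The safeguard describes what the study team does and does not promise that controls stay unaware. Carer ratings are openly labelled unblinded, and teachers provide a blinded rating of the same outcome. This also stands in part: the teacher rating is largely free of the rater bias. It would still register a real dietary change in a TAU sibling.

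A third reply is that the Discussion accepts participants' use of other interventions as noise that affects all interventions equally. That does not cover this case, since diet reaching a TAU sibling falls on the comparator.

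Finally, testing is exploratory and the study is not powered, and the shift calculated above is far below pilot noise. That stands.

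**Conclusion.** The point holds as a minor improvement to the design. The allocation procedure, eligibility criteria and analysis as described contain no household rule. Wherever siblings are split between an offer and TAU, the plan's safeguard for controls can fail and, for nutrition only, treatment can spill over.

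On the assumptions of 1:1:1 allocation and 5–15% of children with an enrolled sibling, about 1–3 of 30 controls would be unmasked. The nutrition SMD would fall from 0.40 to about 0.38 at the very most.

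A reader might infer more than the document supports:

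- **That controls are contaminated.** The document does not show that any siblings enrol, so this is a possibility of unknown frequency.
- **That two thirds of sibling pairs are split between an offer and TAU.** The 2/3 also counts pairs split between homoeopathy and nutrition; the matching figure is 4/9.
- **That both offers contaminate TAU.** Spill-over is plausible for nutrition and depends on uptake; only the unmasking applies to both.
- **That the progression decision or the sizing is materially distorted.** A shift of 0.02 against a half-width of about 0.51 does not do that, and the net direction is uncertain.

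**What to change.** State under Randomisation that eligible siblings in one household are allocated together to the same arm, using the stratum of the first-enrolled (index) child, and that a sibling who enrols later takes the same allocation. This requires a household identifier to be sent with the stratifying factors. Under Statistical analysis, use household-robust standard errors in the regression.

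The costs are small:

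- **Correlation within households.** For a share s of children in pairs with within-household correlation ρ, the variance of an arm mean grows by a factor 1 + sρ. At s = 5–15% this cannot exceed 1.05–1.15, and it is lower for any ρ below 1.
- **Stratum balance.** It becomes slightly less exact, because a sibling may belong to a different age, medication or severity stratum from the index child.
- **Predictable allocation.** A later sibling's arm is known in advance, so eligibility should be settled before the household's allocation is looked up.

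The gain is that no carer receives an offer for one child and not another, and no TAU child shares a home with the nutrition arm through the trial's own allocation.
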